### Interventions

This RCT will recruit 184 patients with mild-to-moderate AD and randomly allocate them to two groups: AG and CG. The AG (*n* = 92) will be treated using acupuncture combined with donepezil hydrochloride 5 mg/day for 12 weeks, while the CG (*n* = 92) will only receive donepezil hydrochloride 5 mg/day for 12 weeks. The two groups will undergo routine clinical treatment throughout the follow-up period. The evaluation time points will be the 12th week, 24th week (follow-up), and 36th week (follow-up) after treatment begins.

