### Objectives

This study protocol aims to describe a clinical trial for evaluating the efficacy and safety of acupuncture with donepezil hydrochloride on cognitive function in patients with AD and to explore the role of acupuncture based on syndrome differentiation (heart qi deficiency, kidney essence deficiency) in the conventional treatment of AD.

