#### Medicine treatment

Patients will receive donepezil hydrochloride 5 mg daily for 12 weeks. During the trial, participants will be prohibited from using other medicines for AD. The test drug was allocated based on the random coding sequence of the test drug and the number of cases. Each research unit will have a trial medication administrator. The investigator will screen qualified participants. After informed consent and writing of the study medical record, the trial medication administrator will arrange participants based on the order of patient visits and drug coding from small to large distributed medicines; further, they will be registered in the “Clinical Trial Drug Use Record Form.”

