### Safety

The participants will be required to undergo the following necessary clinical laboratory tests for excluding any serious disease: blood routine, urine routine, and hepatic and renal functions during the screening stage and post-treatment (week 12). The results of the tests will be recorded to evaluate the safety of this trial. Treatment-related adverse events, including local hematoma, fainting, nausea, dizziness, insomnia, vomiting, or diarrhea, will be recorded in the CRF, including the time point, severity, measures taken, causal relationship with acupuncture treatment, and final outcome. Severe adverse events will be promptly reported to the principal investigator.

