### Statistical methods

All statistical analyses will be performed using SPSS Statistics for Windows V21.0 (IBM SPSS). Three sets of data will be used:Full analysis test (FAS). This will include all randomized cases that underwent assessments at least once for efficacy analysis. Missing data, which may affect analysis, will be supplemented using the last observation data. FAS will be the main population for efficacy evaluation.The protocol set (PPS, per-protocol set). This will include patients that meet the inclusion criteria specified in the trial protocol, complete all observation period plans, and do not use other drugs or treatment measures that may affect efficacy evaluation during the trial period. Efficacy evaluation will be conducted using the FAS and PPS. PPS is a secondary population for efficacy evaluation.Safety analysis data set (SS, safety set). This will include all cases that use the study drug at least once and undergo post-treatment safety evaluation after randomization. The SS will be the main population for safety evaluation.

All statistical tests will be performed as two-sided, and the statistical significance will be set at *p*<0.05. Quantitative indicators will be described using the mean and standard deviation, maximum value, minimum value, and median; moreover, the classification indicators will be described using the number and percentage. For counting data, two-sample tests (including the Cochran-Mantel-Haenszel test) or Fisher’s exact probability method will be used for between-group comparisons; moreover, measurement data will be expressed as mean and standard deviation. One-way analysis of variance will be used for among-group comparisons; additionally, the least significant difference method (LSD-t test) will be used for between-group comparisons.

Demographics (age, sex, duration of illness, education level) and MMSE scores will be compared between the two groups as baseline assessments. The main time point for efficacy evaluation is 12 treatment weeks (for PPS), as well as when the group is discontinued (for the FAS population). The *t*-test will be used for between-group comparisons of other measured efficacy indicators, including analyzing the change from the baseline. The ADAS-cog, MMSE, ADCS-ADL, and QOL-AD will be analyzed using the covariance analysis model for between-group comparisons with the baseline.

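### The main safety set is entered by use of the study drug, which here is donepezil, so a patient who was needled but took no donepezil falls outside it

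*Protocol article*

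**What the plan says.** The Interventions section gives the acupuncture group both treatments ("will be treated using acupuncture combined with donepezil hydrochloride 5 mg/day for 12 weeks"), while the control group "will only receive donepezil hydrochloride 5 mg/day for 12 weeks". Each group has 92 patients. The Objectives describe a trial for "evaluating the efficacy and safety of acupuncture with donepezil hydrochloride on cognitive function in patients with AD".

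Under Statistical methods the safety set is defined as follows: "This will include all cases that use the study drug at least once and undergo post-treatment safety evaluation after randomization". It is given first place for safety: "The SS will be the main population for safety evaluation".

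The Medicine treatment section uses the word drug for the coded, dispensed medicine: "The test drug was allocated based on the random coding sequence of the test drug and the number of cases". Acupuncture is described under its own heading. Nothing in the article extends the term study drug to acupuncture.

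The Safety section lists the events to be collected: "Treatment-related adverse events, including local hematoma, fainting, nausea, dizziness, insomnia, vomiting, or diarrhea, will be recorded in the CRF". Among the details recorded for each event is the "causal relationship with acupuncture treatment".

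**The concern.** A safety set should contain the patients exposed to the treatment whose harms are being assessed. Here the treatment under test is acupuncture, two of the named events (local haematoma and fainting) are typical of needling, and causality is to be judged against acupuncture. The entry condition refers only to the background medicine that both arms take. It reads like a definition carried over from a drug trial.

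At stake is whether every patient who was needled, and every harm from needling, reaches the main safety analysis. For rare serious events the loss of a single patient can matter, because it can turn one event into none.

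**Working it through.** The plan states no figure on this point, so there is nothing to reproduce. The check applies the definition to each possible exposure pattern, assuming in each case that the second condition, a post-treatment safety evaluation, is met.

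| Donepezil dose | Acupuncture session | In the set as written | In the set if either treatment counts |
|---|---|---|---|
| yes | yes | yes | yes |
| yes | no | yes | yes |
| no | yes | **no** | **yes** |
| no | no | no | no |

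**Membership.** Only the third row changes. These patients were needled but are excluded.

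**Effect of losing them.** Let m be the number of patients with both treatments and e the number of these with a needling event. Let c be the number needled without donepezil and f the number of these with an event. As written, the rate among needled patients in the set is e/m; with everyone needled it is (e + f)/(m + c). The event count can only fall, by f. The rate can move either way, depending on whether f/c is above or below e/m. The article gives no basis for c or f, so no size follows. All 184 patients are to receive donepezil, so c should be small.

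**Second row.** This row contains the whole control arm if the plan is followed, so never-needled patients belong in the set. The question is only where an acupuncture-arm patient of this type is counted. If k of the 92 acupuncture patients took donepezil but were never needled, and r is the event rate among needled patients, then:

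- grouped as treated, or with needled patients as the denominator: the reported rate is r, with no dilution;
- grouped by allocated arm: the reported rate is r × (92 − k)/92.

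As an illustration of the second case, assume r = 10%, k equal to 0, 5, 9 or 14 (0% to about 15% of the arm), and all 92 evaluated for safety. None of these values comes from the article.

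- k = 0: 10% × 92/92 = 10.0%
- k = 5: 10% × 87/92 = 9.5%
- k = 9: 10% × 83/92 = 9.0%
- k = 14: 10% × 78/92 = 8.5%

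These figures measure the effect of a grouping rule. They do not measure the effect of the exposure condition: changing that condition to a session or a dose would leave all k patients in the set.

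**The case against.** The strongest objection is that this is a gap in wording with little practical consequence. Everyone is to receive donepezil, so a patient needled without a single dose should be rare. Study drug may also be loose wording for study treatment. The aim concerns acupuncture given with donepezil, and comparing donepezil takers between arms fits that aim. Needling harm is also captured outside the set: patients are observed after each session, adverse events go on the case report form, and severe events are reported promptly to the principal investigator.

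Much of this stands. The effect is probably small, and an excluded patient's event would still be recorded. It would, however, be missing from the population that the plan names as the main one for safety. The article does not say that study drug includes acupuncture, and its other use of drug points to the dispensed medicine.

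A reader might infer more: that never-needled patients are counted as exposed to acupuncture, or that a control patient needled off protocol is counted as not needled. The text does not support this. Being in the safety set is not the same as being classified as needled, and the article does not say whether patients are grouped as randomised or as treated. That rule may be in an analysis plan that is not shown, so its absence is not a fault here. Nor does the 15% dropout allowance support a number of never-needled patients: it covers loss from the trial, and says nothing about patients who stay on donepezil and attend no session.

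**Conclusion.** The point holds in a limited form. The exposure condition of the main safety set is tied to the treatment common to both arms and omits the one under test. Applied literally, it excludes a patient who was needled without taking donepezil, together with any needling harm. This rests on reading study drug as donepezil, which the Medicine treatment section supports and nothing in the article contradicts.

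The effect is probably small and cannot be sized from the article. Dilution of needling-event rates by never-needled acupuncture-arm patients is conditional: it arises only under analysis by allocated arm and only if such patients exist. The point is worth correcting because the stated definition does not fit the design and the correction is simple.

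**What to change.** In the safety-set definition under Statistical methods:

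1. Replace the exposure condition so that the set includes randomised patients who had at least one acupuncture session or at least one dose of donepezil. This brings in the excluded patients.
2. State that patients are grouped by treatment actually received. This settles where never-needled acupuncture-arm patients, and any control patient needled off protocol, are counted.
3. Report needling-related events with patients who had at least one session as the denominator.

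The second and third steps are needed as well as the first, because the wider exposure condition does not by itself remove dilution. The requirement for a post-treatment safety evaluation is a separate matter that this point does not address.

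The cost is a short change of text before analysis. Drug use already has its own record form. The article names no session log, so the team should confirm that the case report form shows whether each patient had at least one session. The one small downside is that needling-event rates may look slightly less favourable.

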### Drop out criteria

The following shedding standards were used to withdraw patients from the study. (1) Subjects who received other treatments of AD drugs during the study period; (2) subjects who did not come to the hospital for follow-up visits on time, and could not be contacted by telephone or SMS; and (3) subjects unwilling to continue to participate in the study, and who voluntarily withdraw their informed consent.

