#### Follow-up

All participants will be treated for 12 weeks. Subsequently, they will enter a 24-week follow-up period. In the 24th and 36th weeks, the patients will be reassessed using the MMSE, Alzheimer’s Disease Cooperative Study-Activities of Daily Living (ADCS-ADL) scale, and Quality of Life-Alzheimer’s Disease (QOL-AD) scale.

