#### Secondary outcome measures

##### ADAS-cog at follow-ups

Participants’ cognitive function will also be assessed using the ADAS-cog scale at week 24 (follow-up) and week 36 (follow-up).

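### Routine care in weeks 12–36 is not reconciled with the ban on other AD drugs, and applying the drop-out rule replaces real week-24 and week-36 scores with carried-forward ones

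*Protocol article*

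**What the plan says.** All references are to the protocol article.

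- **Treatment period.** Medicine treatment: "Patients will receive donepezil hydrochloride 5 mg daily for 12 weeks". Follow-up then adds: "Subsequently, they will enter a 24-week follow-up period". Assessments fall at weeks 24 and 36.
- **Care in follow-up.** Interventions: "The two groups will undergo routine clinical treatment throughout the follow-up period". The article does not say whether this means continued donepezil, another AD drug or something else.
- **Ban.** Medicine treatment: "During the trial, participants will be prohibited from using other medicines for AD".
- **Drop-out rule.** Drop out criteria opens with "The following shedding standards were used to withdraw patients from the study". Criterion (1) is "Subjects who received other treatments of AD drugs during the study period". Criterion (2), in the same list, covers "subjects who did not come to the hospital for follow-up visits on time".
- **Data after drop-out.** Ethics approval and consent to participate keeps the data gathered before a participant drops out. Statistical methods makes the FAS (all randomised with at least one assessment) the main efficacy population and fills gaps with the last observation. The PPS, a secondary population, leaves out users of other drugs that may affect the efficacy evaluation.

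**The concern.** Routine care for AD may come to include a drug other than donepezil; the Background section counts five approved medicines, of which donepezil is one. A participant who receives one between weeks 12 and 36 may simply be on routine care under Interventions, yet is withdrawn under criterion (1). Three hospitals could handle the same event in different ways.

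The statistical harm comes from the consequence of the rule. It ends observation of the participant as well as trial treatment. The trigger occurs after randomisation and is plausibly linked to cognitive decline. It may also be linked to arm, since the Blinding section says that the doctors know the allocation. The scores that go missing are then likely to be informative ones, at the two visits that show whether a difference at week 12 persists.

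**Working it through.** No figure in the plan is disputed, so the main check sets the sections side by side.

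**1. Does the ban reach follow-up?** Medicine treatment limits donepezil to 12 weeks but ties the ban to the trial as a whole. Criterion (1) refers to the study period. Outcome measures uses the same term for the full intervention and assessment schedule, and criterion (2) concerns follow-up visits. So nothing in the wording stops either rule at week 12.

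**2. What triggers withdrawal?** Only another AD drug does. Continued donepezil, or a change in non-AD care, does not.

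**3. What happens to a participant who starts another AD drug at, say, week 16?**

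| Step | Result if criterion (1) is applied |
|---|---|
| Observation | Withdrawn from the study; no week-24 or week-36 score |
| FAS | Retained; the week-12 score stands in at weeks 24 and 36 |
| PPS | Excluded |
| Week-12 primary in the FAS | Unchanged; the score was taken before follow-up began |

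**4. What does the carried-forward score do to the FAS contrast?** In each arm, let p be the share withdrawn in follow-up under criterion (1). Let D be the mean difference, among those participants, between the score they would have had at the visit and the score carried forward. Each arm's FAS mean is then off by −p × D. The between-arm difference (acupuncture minus control) is off by −(p_A × D_A − p_C × D_C). It cancels if the two products are equal and not otherwise. On the ADAS-cog, where higher is worse, a declining participant has D > 0, so the carried-forward score looks too good. The documents give neither p nor D, so neither the size nor the direction of the net error can be calculated.

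**5. How many comparisons are exposed?** ADAS-cog, MMSE, ADCS-ADL and QOL-AD at weeks 24 and 36: 4 × 2 = 8. The secondary outcome sections give 2 (ADAS-cog at weeks 24 and 36) + 3 × 3 (the other scales at weeks 12, 24 and 36) = 11, so 8 of 11 are exposed. The Follow-up section omits ADAS-cog, but the section on ADAS-cog at follow-ups includes it.

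**6. How does this relate to the dropout allowance?** Sample size calculation gives 80 per group, or 160, and 160 × 1.15 = 184. The allowance is thus 184 − 160 = 24 participants. Starting another AD drug is itself a drop-out criterion, so some of these participants may already be inside the 24.

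**The case against.** The strongest reply is that the conflict is conditional. The restrictions cover only other AD drugs, and Interventions never says that routine care includes one. The Discussion presents donepezil alone as consistent with clinical guidelines, so continued donepezil with general care would satisfy all three sections. The ban also comes directly after the 12-week donepezil sentence and could be meant for that phase. This stands against calling it a flat contradiction. It does not remove the gap, because criterion (1) has no such time limit and routine care is undefined.

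A reader might also infer several stronger things that the documents do not support:

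- **Anyone whose routine care changes is lost.** Only another AD drug triggers criterion (1).
- **The main follow-up analysis compares a selected group.** The FAS keeps these participants. Selection applies to the PPS and to any observed-case summary; in the FAS the harm is substituted scores.
- **Drug use in follow-up goes unrecorded.** Neither criterion (1) nor the PPS could be applied without that information, and form content is what an article leaves to the full protocol.
- **A head count of those lost.** Taking 10–30% of the 156 left after 15% dropout (184 × 0.85) gives 16–47. The rates are assumptions, and the sum may count the same people twice (step 6).

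It is fair, too, that the stakes are limited: these are secondary time points, and the Objectives section states no aim about durability.

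**Conclusion.** The point holds as an unreconciled passage combined with a drop-out rule that gives worse follow-up data than necessary. If a participant receives another AD drug after week 12 and criterion (1) is applied as written, observed week-24 and week-36 scores are given up. The FAS then uses an earlier score that can hide decline. Eight secondary comparisons are exposed; the week-12 primary is not.

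The conclusion assumes that some participants do receive another AD drug in follow-up and that sites apply criterion (1) over the whole study period. If routine care is meant to exclude such drugs and nobody takes one, nothing is lost. How often it happens, and whether it differs by arm, cannot be derived from the documents. The finding is a worthwhile, low-cost correction and does not show that the trial's main result is biased.

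**What to change.** 1. **Reconcile** Interventions, Medicine treatment and Drop out criteria: state what routine treatment covers after week 12 and which period the ban covers. The clinical rule is for the sponsor to set.
2. **Separate drug use from assessment.** Change drop-out criterion (1) so that receipt of another AD drug is recorded as an event, with its date, and does not end assessment. Whether such use is allowed remains a matter for item 1.
3. **Keep scoring.** Carry out the week-24 and week-36 scales in all randomised participants who still consent.
4. **Use the observed scores.** In the FAS follow-up comparisons, analyse them as randomised in place of carried-forward values. Keep the PPS as the secondary analysis.
5. **Label the result** as the effect of 12 weeks' treatment followed by routine care.

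The cost is a protocol clarification and one recorded item at two visits that already exist. The downside is that the follow-up contrast then includes any changes in routine care, which the report must say. The article expects the study to end in June 2022 and was published in August 2022, so some follow-up visits may already be past. For those, the report can still give, by arm, the number withdrawn under criterion (1) and the number of week-24 and week-36 values carried forward.

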#### Acupuncture treatment

The main acupuncture points will be GV 20, GV 24, EX-HN 1, EX-HN 3, GB12, GB39, and KI6 (acupoint location; see Table 1). Doctors will be instructed to select the combined acupoints based on traditional Chinese medicine (TCM) syndromes which are based on the TCM syndrome differentiation and diagnosis standard term reference literature [41]. Heart qi deficiency includes forgetfulness (required), indifferent expression, slow response, incomunicative, sleepy, low voice, easy to startle (with 3 or more of the above), pale complexion, and weak pulse. Kidney essence deficiency includes forgetfulness (required), sluggishness, wrong operation, loss of fluency, head tilt and back bending, and fecal and urine incontinence (three or more of the above), the pulse is thin and weak.

**Table 1 Tab1:** Acupoints selected in the study

Acupoints	Location
Shenting (GV 24)	On the head, 0.5 B-cun superior to the anterior hairline, on the anterior median line.
Yintang (EX-HN 3)	At the midpoint of the line joining the medial ends of both eyebrows
Baihui (GV 20)	On the head, 5 B-cun superior to the anterior hairline, on the anterior median line.
Sishencong (EX-HN1)	On the top of the head, 1cun before and after GV20 on both sides with a total of 4 points
Wangu (GB12)	In the anterior region of the neck, in the depression posteroinferior to the mastoid process.
Zhaohai (KI6)	On the medial aspect of the foot, 1 B-cun inferior to the prominence of the medial malleolus, in the depression inferior to the medial malleolus.
Xuanzhong (GB39)	On the fibular aspect of the leg, anterior to the fibula, 3 B-cun proximal to the prominence of the lateral malleolus.
Shenmen (HT7)	On the anteromedial aspect of the wrist, radial to the flexor carpi ulnaris tendon, on the palmar wrist crease.
Neiguan (PC6)	On the anterior aspect of the forearm, between the tendons of the palmaris longus and the flexor carpi radialis, 2 B-cun proximal to the palmar wrist crease.
Taixi (KI3)	On the posteromedial aspect of the ankle, in the depression between the prominence of the medial malleolus and the calcaneal tendon.
Shenshu (BL23)	In the lumbar region, at the same level as the inferior border of the spinous process of the second lumbar vertebra (L2), 1.5 B-cun lateral to the posterior median line.

The combined acupoints of HT7 and PC6 will be applied to patients with syndromes of heart qi deficiency, while KI3 and BL23 will be applied to patients with kidney essence deficiency syndrome.

The patient is in the supine position. After disinfection, disposable stainless steel needles (0.25mm×40mm) will be used to pierce the scalp or skin surface rapidly at a 15° angle on the head or 90° on the limbs and trunk. After the needle is inserted to the prescribed depth, the needle will be twisted for about 30s for a feeling of De Qi, such as sourness, numbness and heaviness. The patients will receive treatment 30 min per session, thrice per week (every other day) for 12 weeks. Meanwhile, electro-stimulation will be applied for GV20 and GV24 acupoints (2/50 Hz, dilatational wave). All treatment will be carried out by a well-skilled senior acupuncturist.

After each acupuncture treatment, the doctor will carefully observe whether the patient has pain, subcutaneous hematoma, and other discomfort. After the treatment, the patient will be observed in the clinic for 15 min.

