**Methods/design:**

This multicenter randomized controlled trial commenced on February 1, 2019, at the Shanghai Longhua Hospital of TCM, Shanghai Huashan Hospital of Fudan University, and Shanghai Mental Health Center, and will conclude on June 30, 2022. The study will recruit 184 patients randomly divided into an acupuncture group or a control group at a 1:1 ratio. All participants will receive donepezil hydrochloride (5 mg/day), and those in the acupuncture group will receive acupuncture based on syndrome differentiation with donepezil for 12 weeks. The primary outcome will be the post-treatment change in the Alzheimer’s Disease Assessment Scale-cognition score at 12 weeks. The secondary outcomes will be the efficacy scores of the Minimum Mental State Examination, Alzheimer’s Disease Cooperative Research Activity-Daily Life, and Quality of Life-Alzheimer’s Disease. All assessments will be performed at baseline, after treatment (week 12), and at follow-up (weeks 24 and 36).

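### Adverse events are looked for after each of 36 acupuncture sessions in one arm, but no inquiry is described for controls before week 12, so symptoms that both arms can have are unequally likely to be recorded

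*Protocol article*

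**What the plan says.** **Acupuncture arm.** The Acupuncture treatment section of the Protocol article sets the session schedule: "The patients will receive treatment 30 min per session, thrice per week (every other day) for 12 weeks". It then requires an observation each time: "After each acupuncture treatment, the doctor will carefully observe whether the patient has pain, subcutaneous hematoma, and other discomfort". A stay in the clinic follows: "After the treatment, the patient will be observed in the clinic for 15 min".

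**Control arm.** Under Interventions, controls "will only receive donepezil hydrochloride 5 mg/day for 12 weeks". No sham sessions or contact-matched visits are described.

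**Both arms.** The same section fixes the assessments: "The evaluation time points will be the 12th week, 24th week (follow-up), and 36th week (follow-up) after treatment begins". The abstract gives the same schedule plus baseline. The Safety section places the laboratory tests at screening and week 12, without distinction by arm. On symptoms it says: "Treatment-related adverse events, including local hematoma, fainting, nausea, dizziness, insomnia, vomiting, or diarrhea, will be recorded in the CRF".

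**Analysis.** Statistical methods defines a safety set that covers both arms and names the Cochran-Mantel-Haenszel or Fisher's exact test for between-group comparison of counts. It does not set out a specific adverse-event comparison.

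**The concern.** The list in the Safety section mixes two kinds of event. Local hematoma belongs to needling. Nausea, dizziness, insomnia, vomiting and diarrhea can occur in either arm, and the Introduction itself names all of these except dizziness among the adverse effects of drugs for Alzheimer's disease. For the second kind a between-arm comparison is meaningful, and it needs the same chance of detection in both arms.

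As described, a mild symptom in an acupuncture patient can be noticed within days. In a control patient the first described opportunity is week 12, and it depends on recall by a person with dementia (inclusion MMSE scores between 11 and 26) or by a caregiver. With equal true rates, the acupuncture arm would tend to show more events.

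Two things are at stake. Safety is part of the stated objective. The Introduction also cites reduced medication side effects as a possible benefit of acupuncture, and this bias would tend to hide such a benefit. An analysis plan cannot repair it afterwards if control events were not asked about.

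**Working it through.** The plan states no adverse-event rate and no figure to reproduce, so the check has two parts: what the schedule implies, and an illustration with assumed values.

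**1. Described opportunities for detection, baseline to week 12**

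- Acupuncture: 3 sessions per week × 12 weeks = 36 checks (Acupuncture treatment), plus the week-12 evaluation.
- Control: the week-12 evaluation only (abstract, Interventions, Safety).

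The direction of the bias follows from this imbalance. Its size depends on how many events each schedule captures.

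**2. Illustration**

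Inputs:

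- n = 92 per arm (Interventions).
- Fisher's exact test, two-sided 5% (Statistical methods).
- Same true event risk p in both arms: assumed 5%, 10% or 20%.
- Capture probability with acupuncture dA = 0.95: assumed.
- Capture probability in controls dC = 0.40, 0.60 or 0.80: assumed.

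Recorded risk ratio with no true difference = (p × dA)/(p × dC) = dA/dC:

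- 0.95/0.40 = 2.4
- 0.95/0.60 = 1.6
- 0.95/0.80 = 1.2

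Expected recorded counts at p = 20%: acupuncture 92 × 0.20 × 0.95 = 17.5; control 92 × 0.20 × dC = 7.4, 11.0 and 14.7.

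Chance of a false significant excess in the acupuncture arm, from summing the two binomial distributions over all tables with Fisher p < 0.05 and more events with acupuncture:

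| True rate | dC = 0.40 | dC = 0.60 | dC = 0.80 |
|---|---|---|---|
| 20% | 52% | 20% | 5% |
| 10% | 22% | 9% | 3% |
| 5% | 7% | 3% | 2% |

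For reference, the same calculation with equal capture of 0.95 in both arms gives 1.6%, 1.4% and 0.9% at true rates of 20%, 10% and 5%. Fisher's test is conservative here, and the excess over these values is the effect of unequal capture.

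**3. Masking of a true benefit**

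A true reduction with acupuncture is recorded as no difference when it equals 1 − dC/dA. That is 1 − 0.40/0.95 = 58% at the low end of control capture and 1 − 0.80/0.95 = 16% at the high end.

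**The case against.** **Controls may be seen before week 12.** A reader might infer that controls have no scheduled contact at all before week 12. The document does not say so. The abstract and Interventions list evaluation points, not every contact. Table 2, which should show the intervention and assessment times, is not visible. Medicine treatment describes dispensing without giving intervals, and the drop-out criteria mention telephone and SMS contact. An article may leave the visit calendar to the full protocol. This stands, and the point is limited to what is described: an active check at every session in one arm and no stated counterpart in the other. Occasional dispensing visits would narrow the gap but not close it; monthly visits, for example, would still set about 3 contacts against 36.

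**The session check is about needling.** It sits under the acupuncture procedure and names pain and hematoma first. Watching for these in one arm only is proper. This stands in large part, and it is a reason not to treat the 36 checks as 36 full symptom inquiries. But the wording also covers other discomfort without limit, and a patient seen three times a week has many occasions to mention nausea or poor sleep.

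**The whole safety comparison is not at issue.** A reader might conclude that it merely reflects how often patients are seen. That goes too far. Laboratory tests are timed alike in both arms, and needling injuries cannot arise in controls. For shared symptoms, contact frequency distorts the comparison without wholly determining it.

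**The size is assumed.** This is correct. At low event rates, or with good recall in controls, the effect is small. A normal approximation gives larger figures at a 20% rate (about 8% to 60%), but the plan names Fisher's exact test, so the smaller exact figures are the ones to use.

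**Conclusion.** The concern holds for shared symptomatic events only. The plan as described gives nausea, dizziness, insomnia, vomiting and diarrhea a better chance of being recorded in the acupuncture arm, and a between-arm comparison of them is biased toward an apparent excess there. This conflicts with the aim stated under Blinding that the arms be handled alike apart from treatment.

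The direction rests on the described schedule. It would weaken if Table 2 or the full protocol shows equivalent inquiries for controls. The size rests on assumed capture and event rates: the chance of a false significant excess runs from about 2% to 52% over true rates of 5% to 20%, so it may be negligible or serious. The primary outcome is untouched.

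**What to change.** State that the between-arm comparison of shared symptoms uses only events elicited with the same checklist, put to patient and caregiver in both arms at the same time points. The existing week-12 visit is the minimum; brief interim calls to both arms can be added if feasible. Keep the observation after each session unchanged, and report what it finds in a separate table that describes needling safety. If the full protocol already provides for equal inquiry in both arms, say so in the text.

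The week-12 version adds no visit and leaves treatment unchanged; interim calls would cost some site staff time. The CRF already records the time point of each event, which helps to keep session-observed events apart from those elicited at week 12. The downside is that session-observed events leave the comparative table, and recall at week 12 misses some mild events, but it does so on the same footing in both arms.
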